## Methods/design

### Design

This pilot study is a randomized, controlled, multi-center, clinical trial. The study will be sequentially conducted as follows: enrollment after screening via inclusion and exclusion criteria; randomization; a treatment period of 12 weeks; and assessment. The flow chart of the study is shown in Figure 1.

**Figure 1 F1:**
[figure not shown]
Flow chart of the clinical study.

### Participants and eligibility

### Inclusion criteria

To be included in the study, patients must have:

1. symptoms of diabetes and a casual plasma glucose ≥11.1 mmol/L or fasting plasma glucose ≥7.0 mmol/L or in a oral glucose tolerance test, two-hour plasma glucose ≥11.1 mmol/L;

2. 30 mg/g < albumin-to-creatinine ratio (ACR) <300 mg/g or 30 mg/24hour <24 hour UAE <300 mg/24 hour, and GFR ≥40ml/min;

3. an age of 18 to 75 years;

4. acceptable glycemic control (FPG ≤10.0 mmol/L or postprandial plasma glucose ≤12 mmol/L and HbA1c ≤8.5%);

5. tolerablity to ARBs and blood pressure (BP) <150/90 mm Hg;

6. plasma albumin ≥30g/L

7. provided written informed consent.

The first two criteria must be met simultaneously.

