### Outcome measures

#### Primary outcome

The primary outcome, percentage change in ACR from baseline, will be measured at week 12. ACR will be measured with a spot urine test, every four weeks; 15 to 20 ml spot urine samples will be collected at each visit to assess albuminuria.

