### Statistical methods

Statistical analyses will be conducted based on an intention-to-treat population. Participants who take at least one dose of drug and have one value on treatment comprise the full-analysis set (FAS) and those who complete a 12-week treatment comprise the per-protocol set (PPS). Missing data will be imputed with the use of the last-observation-carried-forward method, whereby missing values will be replaced by the last non-missing value. Repeated measures and multivariate analysis of variance of the general linear model will be applied to determine the changes in GFR, Scr and FPG at each visit. Percentage reduction from baseline in ACR and changes from baseline in HbA1c will be summarized and comparisons will be made by using a one-way analysis of variance.

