### Sample size

Each arm will only include 12 subjects, for this is just a pilot trial aimed at exploring some parameters for a future clinical trial with a large sample size.

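### Entry on 24-hour albumin excretion alone allows a baseline spot ACR below 30 mg/g, the denominator of the primary outcome, so one patient can shift a 12-patient arm mean by about 25 points

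*Protocol article*

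**What the plan says.** Under Inclusion criteria, item 2 of the protocol article joins two albuminuria ranges as alternatives: "30 mg/g < albumin-to-creatinine ratio (ACR) <300 mg/g or 30 mg/24hour <24 hour UAE <300 mg/24 hour". The closing sentence, "The first two criteria must be met simultaneously", ties item 1 (diabetes) to item 2. It leaves the choice inside item 2 open. No other inclusion or exclusion criterion bounds the spot ACR.

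The Primary outcome section says: "The primary outcome, percentage change in ACR from baseline, will be measured at week 12". The specimen is spot urine: "ACR will be measured with a spot urine test, every four weeks".

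Statistical methods keeps the outcome on the percentage scale ("Percentage reduction from baseline in ACR and changes from baseline in HbA1c will be summarized") and states that "comparisons will be made by using a one-way analysis of variance". That section states no log scale and no adjustment for baseline ACR.

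On size, the Sample size section says: "Each arm will only include 12 subjects, for this is just a pilot trial".

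**The concern.** The measure that admits a patient need not be the measure that is analysed. UAE and spot ACR are different quantities, so someone with a UAE just above 30 mg/24 hours can have a spot ACR below 30 mg/g. That low ACR then becomes the denominator of the primary outcome, and a modest absolute rise turns into a very large percentage.

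With 12 patients per arm, one such value can offset the response of the other 11. The Objective section asks three comparative questions: granule against decoction, the working dose, and granule against irbesartan. All depend on arm means of this outcome. The Sample size section adds that the pilot should supply parameters for a larger trial. The SD of the primary outcome is an obvious one, and a few low-baseline patients can inflate it.

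**Working it through.** **What can be reproduced.** The article gives no alpha, power, effect size or SD, so there is no sample-size calculation to reproduce. Its arm sizes are consistent: 4 × 12 = 48.

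**Leverage of one patient.** Percentage change = 100 × (week 12 / baseline − 1).
- From 10 to 40 mg/g: 100 × (40/10 − 1) = +300%. Compared with no change in that patient, the arm mean moves 300/12 = 25 points.
- If the other 11 patients are at −30% (assumption), the arm mean is (11 × (−30) + 300)/12 = −2.5% instead of −30%, a shift of 27.5 points.
- From 20 to 60 mg/g (+200%): (−330 + 200)/12 = −10.8%, a shift of 19.2 points.

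**Same absolute rise of 30 mg/g at different baselines.** 10: +300%. 31: +97%. 100: +30%. 300: +10%. 600: +5%.

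**High baselines, other 11 at −30%.** From 600 to 300 (−50%) the mean moves −1.7 points. From 400 to 40 (−90%) it moves −5 points. A doubling from 600 moves it 10.8 points, exactly as a doubling from 31 or 100 does. There is no extra leverage above 300 mg/g.

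**In-range baselines.** From 31 to 124 mg/g is also +300% and also shifts the mean 27.5 points. The skew exists without UAE entry.

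**How often, and how much in total?** The article gives neither the variability of spot ACR nor its disagreement with UAE, so both were assumed in a simulation:
- long-run albuminuria lognormal, median 90, between-patient log SD 1.0;
- patient-level difference between ACR and UAE, log SD 0.3;
- UAE measurement log SD 0.3;
- spot ACR within-patient log SD 0.3, 0.5 or 0.7;
- true week-12 ratio 0.70, with no variation in response;
- the ACR used for entry is also the baseline ACR.

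| Spot log SD | Baseline ACR ≤30 under the either-measure rule | Chance of at least one in an arm of 12 | Mean % change, ACR ≤30 | Mean % change, ACR in range | SD of % change, either measure | SD, ACR range required | Cut in SD |
|---|---|---|---|---|---|---|---|
| 0.3 | 6.2% | 54% | −2 | −24 | 34.1 | 33.3 | 2% |
| 0.5 | 8.6% | 66% | +47 | −12 | 72.7 | 67.9 | 7% |
| 0.7 | 11.4% | 77% | +133 | +7 | 147.8 | 125.3 | 15% |

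The chance column is 1 − (1 − p)^12. The SE of a 12-patient arm mean falls from 9.8 to 9.6, from 21.0 to 19.5, and from 42.7 to 36.3 points. Adding a between-patient response log SD of 0.3 leaves the cuts at about 2%, 6 to 7% and 16%.

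The in-range column shows the skew on its own. The true reduction is 30% throughout, yet the arithmetic mean reads −24, −12 or +7.

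**On the log scale.** Regressing week-12 log ACR on baseline log ACR in the same simulation gives these residual SDs, either measure against ACR range required: 0.416 and 0.416, 0.669 and 0.673, 0.899 and 0.910. With that analysis the entry restriction gains no precision.

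**The case against.** The strongest reply is that entry on UAE follows the article's own definition. Its Background section grades microalbuminuria by UAE, 30 to 299 mg/24 hours, and the Objective names patients with microalbuminuria. This stands: the criterion is consistent with the rest of the article, and a UAE-qualified patient belongs to the target population.

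The second reply is that the scale of analysis, not the entry rule, does most of the harm. This stands too. A fourfold rise from 31 mg/g does the same damage as one from 10 mg/g, and the entry rule accounts for only a small part of the simulated spread at a log SD of 0.3 to 0.5. What remains is that UAE-only entry adds patients selected for a low spot value. These tend to drift upward on re-measurement, which is why their mean change differs so much from that of in-range patients.

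Third, randomisation spreads such patients across arms by chance, so no arm is systematically favoured. That is correct. The cost is extra variance and chance imbalance in small arms.

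A reader might infer more than the article supports:
- That any ACR outside 30 to 300 mg/g can dominate an arm. Percentage change is scale-free and a fall cannot exceed 100%, so high baselines do not have this effect.
- That a normal ACR has no room to fall. From 20 to 10 mg/g is −50%, the same as from 200 to 100.
- That the endpoint rests on one untimed sample at each end. The article says "15 to 20 ml spot urine samples will be collected at each visit to assess albuminuria" and fixes neither the number of samples nor the time of voiding. Such details may sit in the full protocol.

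**Conclusion.** The point holds as a modest design weakness on the low side only. The article permits a baseline spot ACR below 30 mg/g and divides the primary outcome by it, on an unlogged scale, in arms of 12. The 25-point shift is plain arithmetic on an illustrative patient; how often such a patient occurs is not known from the article. Under the assumptions above, an arm has a 54 to 77% chance of including at least one patient at or below 30 mg/g, though most will be less extreme than the example.

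The gain from matching the entry measure to the outcome is a cut of about 2 to 7% in the SD of percentage change for a spot log SD of 0.3 to 0.5, and about 15% at 0.7. It is tempting to see a contradiction between eligibility and outcome, or the main cause of noise in the endpoint, but the article supports neither. The larger problem is the arithmetic percentage scale, which the entry rule makes somewhat worse.

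**What to change.** 1. **Entry, for remaining recruits.** Reword criterion 2 so that the baseline spot ACR itself must meet the existing ACR range, with UAE as supporting evidence only. The part that matters here is the lower bound, above 30 mg/g. This is a one-line amendment. In the simulation it loses about 6 to 9% of otherwise eligible patients at a spot log SD of 0.3 to 0.5 if only the lower bound is enforced, and about 12 to 17% if the full range is (6.2 + 5.7 and 8.6 + 7.9, the second terms being patients at or above 300 mg/g). These shares depend on the assumed disagreement between ACR and UAE.

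2. **Analysis, for all patients.** Analyse log ACR at week 12 with baseline log ACR as covariate, and report geometric mean ratios between arms. A geometric mean ratio of 0.70 still reads as a 30% reduction. The Trial status section says recruitment is under way, so some UAE-only patients may already be enrolled. This analysis keeps them without giving them undue weight, and it costs nothing in data collection. It is the more important change; once it is in place, the entry restriction adds little.

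3. **Optional and separate.** Averaging two urine samples at baseline and at week 12 would improve precision on the log scale. With variance 2 × s²/k + 0.3² for k samples, and assumed s of 0.3 to 0.5, the SD of change falls from 0.52–0.77 to 0.42–0.58, a variance ratio of 1.5 to 1.7. If one sample per visit is otherwise planned, that is 48 × 2 = 96 extra assays. Both variances are assumed, and this gain does not bear on the entry criterion.

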### Exclusion criteria

Patients will be excluded if they have any of the following:

1. diabetes mellitus concurrent with non-diabetic kidney disease or are kidney transplant recipients;

2. concurrent severe disorders of heart, brain, liver or the hematopoietic system;

3. newly diagnosed or relapsed tumors;

4. mental disorders;

5. intolerance to oral medications or severe malabsorption;

6. hepatic dysfunction or a value of transaminase higher than one and a half times the upper limit;

7. allergy to TCM/ARBs or other allergies;

8. uncontrollable urinary infection or infections which influence the measurement of urinary protein;

9. pregnancy or lactation;

10. participation in other clinical trials within the past thirty days; and

11. anticipated survival <1 year.

### Recruitment

There are six centers involved in this clinical trial and participants will be recruited via posters at each participating center.

### Randomization and intervention

The study has four arms. After enrollment, 48 participants who meet the inclusion criteria will be randomly assigned to either: 1) granule group, 10 grams three times daily (G10 group, n = 12); 2) granule group, 20 grams three times daily (G20 group, n = 12); 3) the decoction group (D group, n = 12); or 4) the irbesartan group (Aprovel group, n = 12). The treatment course is 12 weeks. The randomization sequence will be generated with an SAS software package by the Good Clinical Practice (GCP) Center of the Teaching Hospital of Chengdu University of TCM and will be concealed and disseminated using opaque envelopes.

### Outcome measures

#### Primary outcome

The primary outcome, percentage change in ACR from baseline, will be measured at week 12. ACR will be measured with a spot urine test, every four weeks; 15 to 20 ml spot urine samples will be collected at each visit to assess albuminuria.

#### Secondary outcomes

The secondary outcomes include changes in GFR, Scr, HbA1c, urinalysis and FPG. All of these will be measured every four weeks except for HbA1c, which will be measured at week 12 only.

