### Compliance

Establishment of TCM and irbesartan after each visit will be quantified in order to enhance medication compliance. Participants whose compliance with TCM or irbesartan is < 80% of the total dose will be considered to have dropped out.

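### HbA1c has no on-treatment value before week 12, so the carry-forward rule, read literally, can only carry the pre-treatment value and impute a change of zero

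*Protocol article*

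**What the plan says.** Three statements in the protocol article bear on this.

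- **Schedule (Secondary outcomes).** After listing GFR, Scr, HbA1c, urinalysis and FPG, the article says: "All of these will be measured every four weeks except for HbA1c, which will be measured at week 12 only". ACR, the primary outcome, is also taken every four weeks.
- **Missing data (Statistical methods).** "Missing data will be imputed with the use of the last-observation-carried-forward method, whereby missing values will be replaced by the last non-missing value". No variable is exempted, and nothing prevents a baseline value from being the one carried forward.
- **Analysis (Statistical methods).** For HbA1c, "changes from baseline in HbA1c will be summarized and comparisons will be made by using a one-way analysis of variance".

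Who is analysed is set in the same section: "Statistical analyses will be conducted based on an intention-to-treat population", and then "Participants who take at least one dose of drug and have one value on treatment comprise the full-analysis set (FAS"). The variable that must have an on-treatment value is not named. A per-protocol set of patients completing 12 weeks is also defined. The Compliance section adds: "Participants whose compliance with TCM or irbesartan is < 80% of the total dose will be considered to have dropped out".

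**The concern.** For ACR, FPG, Scr and GFR, carry-forward can use a week-4 or week-8 measurement, so it keeps some information about response to treatment. For HbA1c the schedule provides none. The only earlier value is the pre-treatment one, which the eligibility criterion on glycaemic control refers to and which a change from baseline presupposes.

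For HbA1c the rule is therefore baseline carried forward under another name. The imputed zero enters the analysis of variance as if it had been observed. If arms lose different numbers of patients, the HbA1c comparison partly becomes a comparison of drop-out. The pull is towards zero in either direction, so a true rise in HbA1c would be hidden as readily as a fall.

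**Working it through.** The article gives no HbA1c effect, SD, drop-out rate or power calculation, so there is no planned figure to reproduce. The only design number that can be checked is 4 arms x 12 = 48, which agrees.

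**Inputs from the article:** 12 patients per arm; HbA1c on treatment at week 12 only; carry-forward without exception; change from baseline compared by one-way analysis of variance.

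**Assumed inputs:** true mean change D of -0.4, -0.8 or -1.2 HbA1c points; k leavers per arm, all in the full-analysis set; leavers would have had the same mean change as completers; SD of change 0.8 where a simulation is used.

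**Step 1: one leaver.** Imputed change = baseline - baseline = 0.

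**Step 2: arm mean.** [(12-k) x D + k x 0] / 12 = D x (12-k)/12. The factor is 0.917, 0.833, 0.75 and 0.667 for k = 1, 2, 3 and 4. At D = -0.8, k = 2 gives -0.67 and k = 3 gives -0.60.

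**Step 3: false difference between two equally effective arms.** Size = |D| x (k1-k2)/12.

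| True change | 3 v 0 leavers | 2 v 2 leavers |
|---|---|---|
| -0.4 | 0.25 x 0.4 = 0.1 | 0 |
| -0.8 | 0.25 x 0.8 = 0.2 | 0 |
| -1.2 | 0.25 x 1.2 = 0.3 | 0 |

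If D = 0, every entry is 0.

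**Step 4: if leavers differ from completers.** Suppose leavers would have shown a fraction f of the completers' change. The false part is then f x |D| x (k1-k2)/12. At D = -0.8, 3 v 0 leavers and f = 0.5, it is 0.5 x 0.2 = 0.1. At f = 0 the imputed zero is right on average and nothing is false.

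**Step 5: effect on the test.** The four-arm analysis of variance was simulated at a nominal 0.05 level, with equal true change in all arms and leavers in one arm only.

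- 3 v 0 leavers: false-positive rate about 0.06 at -0.4, 0.07 to 0.08 at -0.8, and 0.10 at -1.2.
- 4 v 0 leavers: about 0.07 at -0.5 and 0.12 at -1.0.
- Observed values only, with leavers missing at random: about 0.05 throughout.

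With a real change of -1.0 in one arm, none in the others, and 4 of 12 lost in that arm, the estimated difference is -0.67 under carry-forward and -1.00 with observed values. Power is 0.48 against 0.72.

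**The case against.** **The text never says that baseline is carried forward.** The full-analysis set requires an on-treatment value. Read variable by variable, that removes a leaver from the HbA1c analysis, so no zero is created. This stands as a possible reading. The article does not adopt it, and on that reading the imputation rule does nothing for HbA1c, so the sentence still needs correcting. Patients with no on-treatment value of anything are outside the full-analysis set on either reading. A reader might infer that every early leaver is given a zero; the text does not support that.

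**A condensed article leaves detail to the full protocol or SAP.** This stands for samples at a withdrawal visit. The article describes no such visit, so the absence of an HbA1c at withdrawal is not a finding. It does not stand for the carry-forward rule, which is stated without exception; a later document would have to override it.

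**The per-protocol set gives a check.** Patients who complete 12 weeks should have an observed week-12 HbA1c. That exposes the problem but does not repair the analysis in the declared main population.

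**The size rests on assumptions and is small against pilot noise.** This largely stands. At an assumed SD of 0.8, the standard error of a difference between two arms of 12 is 0.8 x sqrt(2/12) = 0.33, so a false difference of 0.2 is about 0.6 standard errors. Some shrinkage may also be real: a patient who stops early need not show the full week-12 change.

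**The SD for the larger trial.** A reader might infer that the zeros spoil the SD that this pilot passes on. With 3 of 12 zeros, SD = sqrt(0.75 x 0.64 + 0.75 x 0.25 x D^2), which is 0.71, 0.77 and 0.87 for the three assumed changes. Against 0.80 that is about -11%, -3% and +8%, whereas the sampling error of an SD from 12 patients is roughly 20%. The article also does not name an HbA1c SD among the parameters sought. That claim is not made here.

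**Conclusion.** The point holds in a limited form. Taken together, the HbA1c schedule and the unrestricted carry-forward rule mean that, on the literal text, a patient analysed without a week-12 HbA1c contributes a change of exactly zero. This is a stated rule that gives an uninformative result, not a missing detail.

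The false difference is 0.1 to 0.3 points for 3 v 0 leavers and assumed true changes of -0.4 to -1.2. It requires that the leavers are in the full-analysis set, that they would have changed as completers did, and that drop-out is unequal. A reader might infer that the HbA1c comparison will be biased against the arms that lose most patients. The article gives no drop-out or effect figures, so only the possibility is established. Whether patients below 80% compliance would add to the zeros is also open, because the article does not say if their week-12 value is kept.

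HbA1c is secondary, and ACR has four-weekly values, so the primary outcome does not share this particular defect once a week-4 value exists. Importance: minor to moderate.

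**What to change.** 1. **Statistical methods:** exempt HbA1c from the carry-forward rule. Analyse observed week-12 HbA1c with baseline HbA1c as covariate, in place of the one-way analysis of variance on change.
2. **Secondary outcomes:** take the week-12 HbA1c in all randomised patients who can attend, whether or not they are still on treatment. This reduces the missing data and the reliance on leavers resembling completers (step 4 of the working).

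The cost is a change of wording and a week-12 assay in the few patients who have stopped treatment but can still attend. The downside is that somewhat fewer patients enter the HbA1c analysis, which then relies on a missing-at-random assumption for those still without a value. That assumption should be stated.

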**Methods/design:**

A randomized, multi-center pilot trial will be conducted. Forty eight participants with DN will be randomly assigned to one of four treatment groups:

1. A granule group, at 10 grams, three times daily (G10 group, n = 12);

2. A granule group, at 20 grams, three times daily (G20 group, n = 12);

3. A decoction group (D group, n = 12); and

4. An irbesartan group (Aprovel group, n = 12).

The following outcome measures will be used: the percentage change of the albumin-to-creatinine ratio; and the changes in serum creatinine, glomerular filtration rate, fasting plasma glucose and hemoglobulin from baseline to the end of the trial.

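### HbA1c is scheduled for week 12 alone but analysed as change from baseline, and the text neither names the baseline value nor secures one for every participant

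*Protocol article*

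**What the plan says.** Four places in the protocol article bear on HbA1c.

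- **Secondary outcomes, definition:** "The secondary outcomes include changes in GFR, Scr, HbA1c, urinalysis and FPG".
- **Secondary outcomes, schedule:** "All of these will be measured every four weeks except for HbA1c, which will be measured at week 12 only".
- **Statistical methods:** "changes from baseline in HbA1c will be summarized and comparisons will be made by using a one-way analysis of variance". Missing values fall under a general rule: "Missing data will be imputed with the use of the last-observation-carried-forward method".
- **Inclusion criteria, item 4:** "acceptable glycemic control (FPG ≤10.0 mmol/L or postprandial plasma glucose ≤12 mmol/L and HbA1c ≤8.5" (per cent), with no inner brackets to show what the *or* and the *and* join.

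The Abstract (Methods/design) also describes changes in "fasting plasma glucose and hemoglobulin from baseline to the end of the trial". The Abbreviations list expands HbA1c as haemoglobin, so the last item there is most likely HbA1c. That is an inference from the two entries, and the point does not depend on it.

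**The concern.** A change from baseline needs two values. The schedule names one and attaches the word *only* to it. The analysis needs the other, and the article does not say where it comes from. The eligibility screen is the obvious source, but criterion 4 can be read in a way that does not require an HbA1c of everyone, and six centres will be applying it.

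What is at stake is modest but cannot be put right later. The Sample size section says that the pilot exists to supply parameters for a larger trial. If some participants have no pre-treatment HbA1c, the mean and spread of HbA1c change would come from an incomplete part of arms that hold only 12 each. A baseline that was not taken before treatment cannot be obtained afterwards, and the Trial status section reports that recruitment is under way.

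**Working it through.** The plan gives no figure to reproduce for this point. The check sets the sections side by side.

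**Step 1. Schedule against analysis.** Change = HbA1c at week 12 − HbA1c at baseline. Secondary outcomes supplies the first term, and Statistical methods requires both. Followed literally, the two sections conflict.

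**Step 2. Is there an earlier value?** Criterion 4 uses an HbA1c limit, so some HbA1c values are expected before enrolment. It can be grouped in two ways:

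- (fasting or postprandial glucose) and HbA1c: every participant needs a screening HbA1c.
- fasting glucose, or (postprandial glucose and HbA1c): a participant can qualify on fasting glucose, and the criterion does not itself require an HbA1c.

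**Step 3. Combine the readings.**

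| Meaning of the schedule | Grouping of criterion 4 | Baseline HbA1c available? |
|---|---|---|
| Week 12 is the only on-treatment measurement; a baseline test is implied | either | yes, for all |
| Week 12 is the only outcome measurement | HbA1c needed of all | yes, from screening, but nothing designates it as baseline |
| Week 12 is the only outcome measurement | fasting glucose suffices | not guaranteed |

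One combination of the three leaves a gap in the data. A second leaves the reference value undesignated.

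**Step 4. Carrying the last observation forward.** With a single on-treatment HbA1c, a participant who leaves before week 12 has no on-treatment value. If a screening value exists and is carried forward, the change is exactly zero. If none exists, there is nothing to carry. The rule therefore cannot supply a missing baseline.

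**Step 5. Adjusted analysis against change score.** Assume equal HbA1c variance σ² at baseline and week 12, and within-arm correlation ρ.

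- Residual variance of the change: 2σ²(1 − ρ).
- Residual variance of week-12 HbA1c adjusted for baseline: σ²(1 − ρ²).
- Ratio, adjusted to change: (1 − ρ²) / [2(1 − ρ)] = (1 + ρ)/2, which is below 1 for any ρ < 1.
- Price: one residual degree of freedom, from 48 − 4 = 44 to 48 − 5 = 43.

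The change score also over-corrects a chance baseline difference Δ between arms, by (1 − ρ)Δ. The protocol gives no SD. Assuming a between-patient SD of 0.8 to 1.0 percentage points, the standard error of Δ between two arms of 12 is SD × √(2/12), that is 0.8 × 0.408 = 0.33 to 1.0 × 0.408 = 0.41 points. Chance differences of that order are therefore ordinary in arms of this size.

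**The case against.** The benign reading is a natural one. The schedule sentence sets HbA1c against outcomes measured every four weeks, so *only* may mean no interim tests rather than no baseline. The Primary outcome section speaks similarly of the percentage change in ACR being measured at week 12, where a baseline is plainly presupposed. Criterion 4 is readily taken as one glucose measure plus HbA1c, and a participant who qualifies on fasting glucose may have had HbA1c tested anyway. The article is also a condensed account. A visit-by-visit schedule may sit in the full protocol, which is not shown, and the flow chart is not reproduced.

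Most of this stands, and it rules out stronger conclusions that a reader might draw:

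- *The HbA1c change cannot be computed.* Not supported: a screening value exists for at least some participants and, on one grouping, for all.
- *Patients admitted on fasting glucose have no HbA1c.* Not supported: not needing the limit for entry is different from not being tested.
- *The arms will be compared on raw week-12 values, with chance imbalance of 0.33 to 0.41 points.* Not supported as a description of the plan, which does not propose that comparison. The figures rest on an assumed SD.

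The objection does not remove the conflict in wording. This is more than an omission left to a fuller document: the article states a schedule, qualifies it with *only*, and states an analysis which that schedule does not feed. No section resolves the two.

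**Conclusion.** The point holds as an unresolved inconsistency. The stated HbA1c schedule and the stated change-from-baseline analysis do not match, no baseline value is named, and criterion 4 as punctuated does not guarantee a screening HbA1c for everyone. The outcome is computable for all who reach week 12 if a pre-treatment value exists for all.

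The number of participants affected cannot be derived from the article; it may be zero. The effect is confined to one secondary outcome, and the primary outcome and the sample size are untouched. The preference for baseline adjustment rests on the equal-variance assumption in the working, and the gain is small if ρ is close to 1. A correction is worth making now because it is cheap and a missed baseline cannot be recovered.

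**What to change.** 1. In Secondary outcomes, schedule HbA1c *at baseline and week 12*. Alternatively, state that the screening HbA1c is the baseline and that it is measured in every participant.
2. In Statistical methods, replace the unadjusted one-way ANOVA of HbA1c change with an ANCOVA of week-12 HbA1c, with arm as factor and baseline HbA1c as covariate.
3. In inclusion criterion 4, the sponsor should make the grouping of the glucose and HbA1c conditions explicit according to its own intent. This review takes no position on which grouping applies. Item 1 can be met under either, because measuring HbA1c is separate from using it as an entry limit.
4. Check which participants already randomised have a pre-treatment HbA1c, and report the number without one.

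The cost is protocol wording plus at most one routine blood test per participant, so no more than 48 tests. For anyone already randomised without a baseline value, the change cannot restore it.
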